**Figure 2 figure2:**
[figure not shown]
I-Change model [34].

**Figure 3 figure3:**
[figure not shown]
An example of tailored advice about the social influence of the partner.

**Figure 4 figure4:**
[figure not shown]
Screenshot of a webpage of the intervention showing an animated video advice.

**Figure 5 figure5:**
[figure not shown]
Screenshot of a webpage of the intervention showing 2 questions with answer options.

### Tailored Information on e-Cigarettes

Participants in the intervention condition will receive tailored information on e-cigarettes based on 5 items (Do you know what an e-cigarette is? How harmful do you think e-cigarettes are compared to tobacco cigarettes? Do you think e-cigarettes are helpful in quitting smoking? Do you think using e-cigarettes is difficult or easy? Have you seen reports in the media about illnesses and deaths in the United States related to the use of e-cigarettes?). These items were developed by the research team and evaluated for comprehensibility and clarity by a communication expert of the National Institute for Public Health and the Environment. In general, the information will convey the message that, for smokers, the use of e-cigarettes is less harmful than continuing smoking tobacco cigarettes. However, it will be highlighted that this does not mean that using e-cigarettes is harmless. Regarding smoking cessation, it will be stressed that e-cigarettes are especially interesting for smokers who have tried to quit several times but have not succeeded. The possibility to (gradually) decrease the nicotine content of the e-cigarette liquid in order to cope with nicotine withdrawal symptoms will be discussed. The outbreak of lung injury associated with e-cigarette use in the United States of America will be discussed in detail. Participants in the control condition will receive a short text explaining that e-cigarettes are not actively recommended for smoking cessation (“A rather recent method that can be used to quit smoking is the e-cigarette. There is still a lot of uncertainty surrounding the e-cigarette. The e-cigarette is therefore not actively recommended as a method to quit smoking in the Netherlands.”). This short text is aimed to resemble the status quo of communication on e-cigarettes in smoking cessation interventions in the Netherlands.

### Measures

All items of the baseline questionnaire, postintervention questionnaire, and 6-month follow-up questionnaire are reported in Multimedia Appendix 2.

#### Smoking Reduction and Abstinence

The primary outcome of this study will be the number of tobacco cigarettes smoked in the past 7 days [35]. Secondary outcomes will be the average number of tobacco cigarettes smoked per day [36], 7-day point prevalence tobacco abstinence [37], and 7-day point prevalence e-cigarette abstinence [37]. If participants indicate to have used an e-cigarette, the nicotine content of the e-cigarette will be assessed. All outcomes will be assessed at baseline and at 6-month follow-up.

#### Smoking Cessation Methods

The *intention to use a smoking cessation method* (split-up per method) will be assessed directly after the intervention on a 5-point Likert scale ranging from 1=definitely do not to 5=definitely do. At the 6-month follow-up, we will assess which smoking cessation methods were actually utilized (ie, *smoking cessation method chosen*) on a dichotomous scale (yes/no). The following methods will be assessed: face-to-face counselling, eHealth interventions, telephone counselling, group-based programs, nicotine replacement therapy, prescription medication, and e-cigarettes. Participants can also indicate to have used another smoking cessation method or to not have used any smoking cessation method at all.

#### Determinants of Decision Making

Determinants of decision making will be assessed by 2 constructs: knowledge and attitude. Knowledge about e-cigarettes (eg, There are less harmful substances in e-cigarettes compared to tobacco cigarettes) will be measured by 7 items with response options being 1=True, 2=False, and 3=I do not know. Correct answers will be coded as 1 and incorrect answers and the option I do not know as 0. The sum of the correct answers is the overall score for the construct knowledge. Attitude on e-cigarettes (eg, I think that using e-cigarettes is better for my health than smoking cigarettes) will be measured by 10 items on a 5-point Likert scale ranging from 1=I totally disagree to 5=I totally agree. All items will be assessed directly after the intervention.

#### Process Evaluation

A process evaluation will be conducted by assessing an *overall grade* for the intervention [27], asking open questions about positive and negative aspects of the intervention, and by analyzing system usage data [27]. An *overall* g*rade* will be measured by 1 item on a scale ranging from 1=very bad to 10=very good. The open questions (eg, What do you like about the intervention?) will be asked to capture aspects that are perceived as both positively and negatively. The overall grade and the open questions will be assessed directly after the intervention. The time spent on the intervention website and the device (eg, smartphone, tablet, desktop) of the users will be measured using the TailorBuilder software (OverNite Software Europe BV). The time spent on the website will be provided per condition, whereas the device used will be reported for all participants together.

#### Demographics and Smoking Characteristics

We will assess the demographics by asking for *gender* (0=male, 1=female, 3=not on the list), *age*, and *education level* (1=low, 2=intermediate, 3=high). *Addiction level* will be assessed by the Fagerström Test for Nicotine Dependence [38]. The 6 items of the scale will be summed into an overall score ranging from 0 to 10. We will classify the dependence level as 0-2=low, 3-4=moderate, 5-6=strong, and 7-10=very strong. Addiction level will be measured at baseline. The *intention to quit smoking* will be assessed by 2 items. First, participants will be asked when they are planning to quit smoking (1=within 1 month, 2=within 6 months, 3=within 1 year, 4=within 5 years) [39]. Second, participants will be asked to indicate whether they are planning to quit smoking within 1 year on a 5-point Likert scale ranging from 1=definitely do not to 5=definitely do. The intention to quit smoking will be measured at baseline and after the intervention for every participant and at 6-month follow-up for participants who indicated that smoking cessation was not successful.

#### COVID-19 Pandemic and Smoking Behavior

The COVID-19 pandemic coincides with the recruitment and follow-up period of this research project. Participants are influenced by the pandemic in numerous ways, including the information that tobacco smoking may increase susceptibility to and severity of COVID-19 [40]. Thus, we included 15 items about smoking-related beliefs and behavior in times of COVID-19. These items are reported in Multimedia Appendix 3.

### Analyses

The focus of all the analyses will be on the effect size accompanied by the confidence interval [41]. Multiple imputations will be conducted to account for the missing observations at 6-month follow-ups. Sensitivity analyses will be conducted for complete cases and intention-to-treat [42]. The primary outcome (number of tobacco cigarettes smoked in past 7 days) will be tested by analysis of covariance [43,44]. The dependent variable will be the number of tobacco cigarettes smoked weekly at the 6-month follow-up. The number of tobacco cigarettes smoked weekly at baseline will be included as the covariate. The independent variable will be the condition. The average number of tobacco cigarettes smoked per day will be tested similarly. Logistic regression analyses will be performed to assess the effect of the intervention condition and control condition on 7-day point prevalence tobacco abstinence and 7-day point prevalence e-cigarette abstinence. Analyses of variance will be performed to test for differences in the determinants of decision making (knowledge and attitude on e-cigarettes) between conditions. Addiction level will be included as a covariate in additional sensitivity analyses. Previous research suggests that the addiction level needs to be considered when assessing the effectiveness of e-cigarettes for smoking reduction and cessation [45]. The open questions will be analyzed per question. Codes for recurrent themes will be created and reported in a table with example quotes and the number of times a theme was addressed.

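### Baseline e-cigarette use is collected, but no covariate is named for the 6-month e-cigarette abstinence regression; this gives up power in a secondary outcome

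*Protocol article*

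**What the plan says.** Under Smoking Reduction and Abstinence, 7-day point prevalence e-cigarette abstinence is a secondary outcome, and the timing is stated for the whole group: "All outcomes will be assessed at baseline and at 6-month follow-up". The baseline value of this binary outcome is therefore in hand. Participants and Recruitment requires recent tobacco smoking and does not exclude people who already use e-cigarettes.

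The Analyses section treats the outcomes in three ways:

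- **Cigarette counts:** analysis of covariance. For the primary outcome, "The number of tobacco cigarettes smoked weekly at baseline will be included as the covariate". The daily count is handled in the same way.
- **Tobacco and e-cigarette abstinence:** one sentence covers both. Logistic regression is to assess the "effect of the intervention condition and control condition on 7-day point prevalence tobacco abstinence and 7-day point prevalence e-cigarette abstinence". No covariate is named.
- **Knowledge and attitude:** "Analyses of variance will be performed to test for differences in the determinants of decision making (knowledge and attitude on e-cigarettes) between conditions". Determinants of Decision Making fixes their timing: "All items will be assessed directly after the intervention". They have no baseline value.

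The only other covariate mentioned is addiction level: "Addiction level will be included as a covariate in additional sensitivity analyses".

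**The concern.** The section names a baseline covariate where it intends one, and it names none for e-cigarette abstinence. Some participants may already vape at entry, and they are likely to differ sharply from the rest in 6-month use. Their baseline status would then predict the outcome well, and a model without it leaves that variation in the comparison.

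The outcome matters to the trial's question. The intervention is information about e-cigarettes, the Research Goal plans a comparison of dual users, and the Discussion is framed around uptake. Enrolment was 492 against a calculated 687, so an existing predictor should not be given up without reason.

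**Working it through.** **The plan's own figure.** The Sample Size Calculation uses d = 0.2, half-width 0.15 and 95% confidence. Total N = 4 × (1.96/0.15)² × (1 + 0.2²/8) = 4 × 170.73 × 1.005 = 686.3, which rounds up to the stated 687. Enrolment of 492 is (687 − 492)/687 = 28% below it. That target is for Cohen's d, not for a binary outcome, and this point does not alter it.

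**Inputs.** From the article: N = 492 and 1:1 allocation, so 246 per arm. Assumed, because the documents give no figures: baseline use p; 6-month control-arm use u₁ in baseline users and u₀ = 10% in others; conditional odds ratio 1.8. The model is written for use; for abstinence the odds ratio is the reciprocal, with the same power.

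**How strongly baseline predicts the outcome (control arm).** Overall use is m = p·u₁ + (1−p)·u₀. The share of variance explained is R² = p(1−p)(u₁−u₀)²/[m(1−m)]. The expected standard error ratio on the risk-difference scale is √(1−R²).

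| p | u₁ | m | R² | √(1−R²) | simulated ratio |
|---|---|---|---|---|---|
| 10% | 30% | 0.12 | 0.034 | 0.983 | 0.971 |
| 10% | 60% | 0.15 | 0.176 | 0.907 | 0.923 |
| 20% | 60% | 0.20 | 0.250 | 0.866 | 0.865 |
| 30% | 70% | 0.28 | 0.375 | 0.791 | 0.803 |

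The standard error of the standardised risk difference falls by about 3% to 20%. Formula and simulation agree.

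**Power and the odds-ratio scale.** Simulated logistic models with and without baseline use, 1,500 trials per row, N = 492:

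| p | u₁ | log OR (SE), unadjusted | log OR (SE), adjusted | power, unadjusted | power, adjusted |
|---|---|---|---|---|---|
| 10% | 30% | 0.583 (0.257) | 0.609 (0.263) | 62% | 65% |
| 10% | 60% | 0.482 (0.237) | 0.583 (0.263) | 53% | 60% |
| 20% | 60% | 0.450 (0.215) | 0.602 (0.253) | 54% | 67% |
| 30% | 70% | 0.365 (0.195) | 0.591 (0.253) | 45% | 66% |

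A separate simulation gave 59% to 61% in the weakest case and 45% to 65% in the strongest. The gain is therefore roughly 2 to 20 points.

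The standard error of the log odds ratio rises on adjustment. Power still rises because the adjusted model estimates a conditional odds ratio, which is further from 1. In the last row, an odds ratio of 1.8 takes use from 70% to 4.2/5.2 = 80.8% in baseline users and from 10% to 0.2/1.2 = 16.7% in others. Overall use goes from 28% to 0.3 × 0.808 + 0.7 × 0.167 = 35.9%. The marginal odds ratio is (0.359/0.641)/(0.28/0.72) = 1.44, with log 0.365.

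**Validity without adjustment.** Simulated type I error (2,000 trials) was 4.6%, 4.8% and 6.3% unadjusted, against 4.3%, 4.7% and 5.2% adjusted, for the second to fourth rows. The simulation error is √(0.05 × 0.95/2000) = 0.5 points, so the 6.3% needed a check. Under the null, each arm's count is binomial(246, m). Summing the joint probabilities of all pairs of counts that the Wald test rejects gives 4.9%, 4.9% and 5.0%. The 6.3% is simulation noise.

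**Chance imbalance.** The 95% range of the difference in baseline use is ±1.96 × √[4p(1−p)/492]: ±5 points at 10%, ±7 at 20%, ±8 at 30%. Multiplied by (u₁ − u₀), an imbalance at that limit moves the crude difference by 1.1, 2.7, 3.5 and 4.9 points in the four rows. The crude 95% half-widths, 1.96 × the simulated SDs of 3.25, 3.45, 3.86 and 4.13 points, are 6.4, 6.8, 7.6 and 8.1 points. The shifts lie inside them.

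**Knowledge and attitude.** For a covariate with correlation r, the half-width in SD units is 1.96 × √(4/492) × √(1−r²). It is 0.177 at r = 0, 0.176 at 0.1, 0.173 at 0.2, 0.169 at 0.3 and 0.153 at 0.5. The interval is 0.5%, 2%, 5% and 13% narrower. The documents give no value for r.

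**The case against.** The strongest reply is that the logistic sentence is silent on covariates and does not exclude them. A condensed article may leave a secondary outcome's covariates to an analysis plan that is not shown. The sentence also covers tobacco abstinence, which has no usable baseline value because everyone must have smoked in the past 7 days. One short sentence for both outcomes is therefore natural. This stands as a limit: the article cannot be said to have ruled adjustment out. It does not remove the point, because the same section names the baseline covariate for the count outcomes, and naming it here would be a specific improvement at no cost.

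A reader might infer that chance imbalance in vaping biases the unadjusted result. It does not: allocation is random, type I error is kept, and the confidence interval already allows for such imbalance.

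A reader might also infer that adjustment would tighten the reported odds ratio. It would not, and this matters because the article puts its focus on effect sizes with intervals. The gain lies in power and on the risk-difference scale, and the estimand changes from a marginal to a conditional odds ratio.

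Finally, the ANOVA wording is more definite than the logistic sentence, so knowledge and attitude may look like the clearer fault. They are the weaker case: baseline vaping is a proxy for both, and its correlation with them is unknown.

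**Conclusion.** The point holds as an efficiency improvement for one secondary outcome, 6-month e-cigarette abstinence. That the baseline value is collected, that vapers are eligible and that no covariate is named all come from the article. The size does not. The gain of roughly 2 to 20 percentage points in power rests on assumed baseline use, persistence, uptake and odds ratio, with all 492 analysed. If few participants vape at entry, or few of them persist, the gain is near the low end.

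Nothing here supports calling the planned analysis wrong or biased, and the primary analysis is untouched. For knowledge and attitude the likely gain is small, at most about 5% in interval width for correlations up to 0.3.

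**What to change.** In the Analyses section, name baseline 7-day e-cigarette use (yes/no) as a covariate in the logistic regression of 6-month e-cigarette abstinence. State that the adjusted odds ratio is conditional on baseline use. Report beside it a risk difference standardised over the trial population, with its 95% confidence interval. Leave tobacco abstinence without a baseline term, since all participants smoked at entry.

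Adjusting the knowledge and attitude comparisons for baseline e-cigarette use is optional. If it is wanted, it should be specified in advance.

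The cost is a few sentences of analysis text. No new data are collected and the sample size is unchanged. If an analysis plan already lists this covariate, a reference to it in the article is enough.

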### Decision Making on e-Cigarettes

Owing to the uncertainty surrounding e-cigarettes, it is important that smokers have sufficient knowledge about e-cigarettes when deciding whether to use them. An informed choice is often defined based on relevant knowledge and the congruence between attitudes and conducted behavior [20]. These conceptualizations of informed decision making employ cut-off points in order to dichotomize constructs into positive and negative outcomes (eg, sufficient knowledge or not). These cut-off points are chosen arbitrarily, indicating that there is neither evidence for the choice of these cut-off points nor evidence that there is an underlying dichotomy at all [21]. Furthermore, individuals who score values close to the cut-off points but on opposite sites (eg, on a scale from 1-10, if 5 is considered to be the cut-off point, individuals who score values close to the cut-off point but on opposite sites would then for instance score 4.9 and 5.1) are categorized as being very different, while in reality being quite similar [21]. In this research, we will avoid dichotomizing continuous variables by examining the constructs of decision making separately.

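### The main tobacco-abstinence model is described with condition only and addiction level is left to sensitivity analyses, which forgoes a small to modest gain in power

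*Protocol article*

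**What the plan says.** Tobacco abstinence over the past 7 days at 6 months is a secondary outcome (Smoking Reduction and Abstinence: "Secondary outcomes will be the average number of tobacco cigarettes smoked per day [36], 7-day point prevalence tobacco abstinence").

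The Analyses section treats the two kinds of outcome differently:

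- For the primary count outcome it names a baseline adjustment: "The number of tobacco cigarettes smoked weekly at baseline will be included as the covariate". Daily consumption is handled in the same way.
- For abstinence it names condition and nothing else: "Logistic regression analyses will be performed to assess the effect of the intervention condition and control condition on 7-day point prevalence tobacco abstinence". E-cigarette abstinence is covered by the same sentence.
- For dependence: "Addiction level will be included as a covariate in additional sensitivity analyses". The reason follows at once: "Previous research suggests that the addiction level needs to be considered when assessing the effectiveness of e-cigarettes for smoking reduction and cessation".

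Under Demographics and Smoking Characteristics, the dependence scale is summed to a 0-10 score and "Addiction level will be measured at baseline". Intention to quit is also asked at baseline, by two items. Weekly cigarettes are recorded at baseline with the other smoking outcomes.

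**The concern.** The plan gives a reason why dependence bears on cessation, then keeps it out of the main cessation model. The variable is already collected at baseline.

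The baseline value of the outcome cannot help here. Every participant must have smoked in the past 7 days to enter, so baseline abstinence is the same for all. Any adjustment has to come from other baseline predictors: dependence, consumption and motivation. Motivation may vary widely, because eligibility runs to people who intend to quit at any time within 5 years.

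The trial also has little information to spare. It enrolled 492 participants against the 687 that its sample size calculation required, a shortfall of 195/687 = 28% before any loss to follow-up. At stake is some power for a secondary outcome, and how well the main estimate allows for a chance imbalance in dependence or motivation.

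**Working it through.** **The plan's own figure.** Sample Size Calculation gives 687 for d = 0.2, half-width 0.15 and 95% confidence. With N = (z/w)² × (4 + d²/2):

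(1.96/0.15)² × (4 + 0.02) = 686.3, rounded up to 687.

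The figure reproduces. It concerns a standardised mean difference and does not depend on how abstinence is modelled. With 492 the half-width is 1.96 × √(4.02/492) = 0.177.

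**Inputs for abstinence.** From the documents: 492 enrolled and 1:1 allocation, taken as 246 per arm with nobody lost. The documents give neither abstinence rates nor the prognostic strength of addiction level, so both are assumptions:

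- Abstinence 10% vs 18%, or 15% vs 25%.
- One standardised baseline covariate with an odds ratio for abstinence of 0.77, 0.67, 0.50 or 0.33 per SD (weak to strong).

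**Method.** 4,000 simulated trials per scenario, each analysed by logistic regression on condition alone and on condition plus the covariate. Three things are compared: power at two-sided 5%, the SE of the log odds ratio, and the variance of the risk difference averaged over the covariate. The participant equivalent is 492 × (1/variance ratio − 1).

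| Rates | Covariate OR per SD | Power, condition only | Power, adjusted | Variance ratio, risk difference | Equivalent participants |
|---|---|---|---|---|---|
| 10% vs 18% | 0.77 | 0.725 | 0.733 | 0.995 | 3 |
| 10% vs 18% | 0.67 | 0.718 | 0.730 | 0.986 | 7 |
| 10% vs 18% | 0.50 | 0.728 | 0.751 | 0.955 | 23 |
| 10% vs 18% | 0.33 | 0.727 | 0.790 | 0.870 | 74 |
| 15% vs 25% | 0.77 | 0.785 | 0.785 | 0.995 | 3 |
| 15% vs 25% | 0.67 | 0.799 | 0.811 | 0.982 | 9 |
| 15% vs 25% | 0.50 | 0.795 | 0.819 | 0.946 | 28 |
| 15% vs 25% | 0.33 | 0.791 | 0.853 | 0.856 | 83 |

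The gain in power is about 0 to 2 points for a weak to moderate covariate and about 6 for a strong one. Variance falls by about 0.5% to 14%. Gains of a point or less are close to simulation error. At higher assumed rates (25% vs 37%) the strong covariate gives somewhat more: power 0.817 to 0.885, variance ratio 0.836.

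**The odds ratio behaves differently.** At 10% vs 18% and a covariate odds ratio of 0.50, adjustment raises the SE of the log odds ratio from 0.273 to 0.282 and moves the odds ratio from 2.00 to 2.08. At 0.33 the SE goes from 0.273 to 0.295 and the odds ratio from 1.99 to 2.22. The adjusted odds ratio is conditional on the covariate and lies further from 1. Power rises because the estimate moves out by more than its SE grows; the interval itself does not narrow.

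**The case against.** The case for leaving the plan alone is substantial.

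- **Validity.** A condition-only comparison is valid under 1:1 randomisation, the outcome is secondary, and the primary outcome is already adjusted for its baseline value. This stands, and it limits the point to efficiency.
- **The plan does consider addiction level.** The sentence on previous research is the stated reason for the sensitivity analyses and does not promise adjustment in the main model. An addiction-adjusted result will be produced, so an imbalance in dependence would not go unexamined. This also stands: there is an awkward fit between reason and placement, but no contradiction.
- **Silence in a condensed article.** That the model has no covariates at all is inferred from the contrast with the analysis of covariance. That is the natural reading, but only the placement of addiction level is explicit.
- **The focus is on the effect size and its interval.** For a logistic model reported as an odds ratio, adjustment does not tighten that interval. This is correct, and it is why the remedy has to name the effect measure as well as the covariates.

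A reader might go further and infer that the dependence bands, "We will classify the dependence level as 0-2=low, 3-4=moderate, 5-6=strong, and 7-10=very strong", break the plan's own argument against cut-offs. They do not. The sentence in question, "In this research, we will avoid dichotomizing continuous variables by examining the constructs of decision making separately", concerns knowledge and attitude, and nothing in Analyses puts the bands into a model.

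**Conclusion.** A minor improvement that needs no new data. As described, the main tobacco-abstinence model leaves out baseline predictors already in hand, including the one that the plan singles out as relevant to cessation. The cost is about 0 to 6 points of power and about 0.5% to 14% of risk-difference variance at N = 492. These figures rest on the assumed abstinence rates (10% vs 18%, 15% vs 25%), on one covariate of assumed strength and on complete follow-up.

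Three stronger readings are not supported:

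- That precision of the odds ratio is lost. Its SE rises on adjustment.
- That the loss can be read off 1/(1 − R²) − 1, which for an assumed R² of 0.05 to 0.10 gives 5.3% to 11.1%, or about 26 to 55 of 492 participants. That is a linear-model result and does not carry over to a logistic odds ratio, and the documents give no R².
- That the primary analysis of covariance should also gain the addiction score. It already contains baseline weekly cigarettes, and no further gain has been shown.

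**What to change.** Before the 6-month data are analysed, amend the Analyses section for tobacco abstinence only:

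1. Main model: logistic regression on condition with the continuous 0-10 addiction score, baseline weekly cigarettes and one baseline intention-to-quit item. Name which of the two items is used and how it is coded, and state that it is the baseline value, since intention is asked again after the intervention.
2. Report a covariate-standardised risk difference with its 95% confidence interval, beside the odds ratio, which is labelled conditional.
3. Keep the condition-only model as the sensitivity analysis, so that it is settled in advance which result leads if the two differ.

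The primary analysis of covariance stays as it is.

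The cost is a few sentences and no new data. The model can carry the extra terms: at 10% vs 18% there would be about 246 × 0.10 + 246 × 0.18 = 69 abstainers for 4 coefficients besides the intercept, or 6 if the four-category timing item is entered as categories. Recruitment closed in July 2020, so the change should be dated. If the 6-month data have already been analysed, the adjusted model should be reported as post hoc.
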